## Methods

### Trial Design

The study will utilize an effectiveness/implementation hybrid type 1 design for the evaluation [40]. This design was chosen as it allows for simultaneous testing of the intervention, its delivery in target settings, and the potential for implementation in real-world situations; using a setting in which there is already clinical momentum reduces risks with potentially high benefit [40]. This trial will be made operational via the STOP program. Intervention effectiveness will be measured using a two-arm randomized controlled trial. Health care practitioners seeing patients randomized to the intervention arm (Group A) will receive computer alerts when a patient does not meet the national guidelines of nutrition or physical activity. They will then be guided to deliver a brief intervention to the patient. Health care practitioners seeing patients randomized to the treatment-as-usual arm (Group B) will not receive computer alerts for physical activity and fruit/vegetable consumption. The evaluation of implementation will be guided by the RE-AIM framework [41].

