### Inclusion Criteria

When a patient is enrolling in the STOP program, the STOP enrollment survey must be delivered by the health care practitioner using the online STOP portal. At the time of enrolling in the STOP program, patients must also be below the national guidelines for physical activity [48] or fruit/vegetable consumption [49]. A low level of physical activity is defined as engaging in less than 150 minutes of moderate/vigorous exercise per week [48]. A low level of fruit/vegetable consumption is defined as consuming less than 7 servings (women) or 8 servings (men) of fruit/vegetables daily in accordance with the 2007 Canadian Food Guide [49].

Patients must also provide at least one piece of contact information (phone number or email address) to allow for follow up to be conducted at 6 months.

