#### Intervention (Group A)

The STOP portal will be adapted to provide a CDSS for physical activity and/or fruit/vegetable consumption (Figure 1). At the time of enrollment, the CDSS will: (1) screen patients for their physical activity and fruit/vegetable consumption levels, (2) provide health care practitioners with an alert when the patient is not meeting guidelines for physical activity and fruit/vegetable consumption, and (3) guide health care practitioners to intervene with the patient using the following steps.

Step 1 involves risk communication with their patient to raise awareness of the identified risk factors. This includes sharing the information in the alert, which lists the specific risk factors (eg, low levels of physical activity) for the patient, and discussing how each risk factor affects their patient’s health and smoking cessation treatment. The CDSS also includes optional guidance for health care practitioners on how to provide risk communication using the Elicit-Provide-Elicit framework [50]. The guidance message will remind health care practitioners to use positively framed risk communication messages. This was based on the results of the engagement events with STOP participants.

In step 2, a customized self-monitoring resource for the risk factors is provided to patients who want to self-monitor as a part of their smoking cessation treatment. The self-monitoring resource (see Multimedia Appendix 1), which health care practitioners will be able to print or email to their patients, is a 1-page weekly tracking sheet, including the following key features: ability to track multiple behaviors simultaneously on the same page; ability to record the number of cigarettes smoked, in addition to the other behaviors they chose to monitor; and setting weekly goals.

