### Statistical Analysis

Analysis of the primary and secondary outcomes will be performed using the intention-to-treat principle. Patients will be analyzed in the study arm to which they are assigned (control vs intervention group). Descriptive statistics (without testing) will be used to summarize patient-level baseline characteristics in the intervention and control groups.

We will test for a group difference in our primary outcome using a chi-square test. For our secondary outcomes, we will test for group differences in change over time by regressing the 6-month outcomes on the baseline measures and group. We will use linear regression for total exercise time and ordinal logistic regression for total fruit and vegetable consumption.

Although the STOP program comprises many separate clinical sites, analyses using mixed-effects models indicate that any true site effects are quite small. We therefore do not anticipate a need to account explicitly for clustering. However, we will test this by measuring the site-level intraclass correlation, and will analyze our data using random intercept models if deemed to be appropriate.

To understand wider associations between our outcomes and participant characteristics, we will also perform multivariate analyses, including logistic regression for smoking cessation, linear regression for exercise, and ordinal logistic regression for fruit and vegetable consumption. In these models, we will include education, income, substance use, mental health diagnoses, gender, age, and the Heaviness of Smoking Index [57] as independent variables.

Primary and secondary outcomes will only be available from patients who complete a 6-month follow-up survey. As a result, we anticipate that approximately 20% of these will be missing, and that there will also be some missing values in baseline variables. We will address these missing data using multiple imputation with chained equations. Our missing data model will include all 3 outcomes, the variables from our secondary (adjusted) analyses, and auxiliary variables, including smoking status from STOP follow-up assessments performed at 3 and 12 months after baseline (where available), smoking status at the last clinical visit, number of visits, clinical counseling received, and type and duration of NRT prescribed. A statistical analysis plan will specify the number of imputed datasets to be created, the models to be used, and the variables to be incorporated.

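### The exercise and fruit/vegetable outcomes are analysed only in all randomised patients, which dilutes each alert's effect on the behaviour it targets; a below-guideline analysis should be pre-specified beside it

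*Protocol article*

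**What the plan says.** Under Inclusion Criteria, one shortfall is enough for entry: "patients must also be below the national guidelines for physical activity [48] or fruit/vegetable consumption [49". Low activity means "engaging in less than 150 minutes of moderate/vigorous exercise per week". Low fruit/vegetable intake means "consuming less than 7 servings (women) or 8 servings (men) of fruit/vegetables daily".

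Under Trial Design, practitioners of Group A patients "will receive computer alerts when a patient does not meet the national guidelines of nutrition or physical activity". Under Intervention (Group A), the content follows the individual patient. Step 1 has the practitioner share "the alert, which lists the specific risk factors (eg, low levels of physical activity) for the patient". In step 2, "a customized self-monitoring resource for the risk factors is provided to patients who want to self-monitor".

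Under Statistical Analysis, "Analysis of the primary and secondary outcomes will be performed using the intention-to-treat principle". For the two behaviour outcomes the protocol will "test for group differences in change over time by regressing the 6-month outcomes on the baseline measures and group", using a linear model for exercise time and an ordinal logistic model for fruit/vegetable servings. It states no restriction, interaction or subgroup by baseline guideline status. The wider multivariable models add demographic, substance use, mental health and smoking-heaviness variables, but not guideline status.

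**The concern.** Take a patient who already exercises 150 minutes a week or more but eats too few fruits and vegetables. That patient is randomised. In Group A the alert and the customised sheet concern diet, yet the patient also counts in the exercise regression in both arms. The reverse holds for a patient who meets the diet guideline but not the activity guideline. Each group coefficient therefore mixes patients in whom the intervention addressed that behaviour with patients in whom it did not.

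The Discussion says the trial will inform whether decision support of this kind is a suitable way to promote activity and diet interventions. If the only estimate is the diluted one, a null or small result could be read as showing that the alerts do not change behaviour, when part of the explanation is that some analysed patients were never alerted about that behaviour.

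**Working it through.** **Plan's own figure.** The protocol states power only for the primary outcome. A two-sided 5% comparison of 0.26 with 0.30 at 80% power needs 1977 per group without continuity correction and 2027 with it. The stated 1999 lies between them. Inflation for 20% loss gives 1999/0.80 = 2498.75, so 2499 per group, as stated. No power is given for the secondary outcomes, so there is nothing to reproduce for them.

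**Inputs.** From the protocol: entry by either guideline, alert content specific to the patient, all randomised patients analysed, 1999 per group with follow-up. Assumed: the share f already meeting a given guideline (not stated, so a range is shown), no effect on that behaviour in those patients, and equal residual variance in the two kinds of patient. For the ordinal model the algebra is an approximation.

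**Dilution.** Let δ be the effect in targeted patients, σ the residual SD and n the number per group.

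- Effect in all patients: (1−f)δ + f·0 = (1−f)δ.
- z in all patients: (1−f)δ / (σ√(2/n)).
- z in the targeted subset: δ / (σ√(2/[n(1−f)])).
- Ratio: (1−f)/√(1−f) = √(1−f).

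Adjusting for baseline reduces σ but does not remove the factor 1−f, because the model has a single group coefficient for both kinds of patient.

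**Power if the targeted subset has 80%**, which is Φ(2.80·√(1−f) − 1.96):

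| f | 2.80·√(1−f) | Power in all patients |
|---|---|---|
| 0.05 | 2.73 | 78% |
| 0.10 | 2.66 | 76% |
| 0.2 | 2.50 | 71% |
| 0.3 | 2.34 | 65% |
| 0.4 | 2.17 | 58% |
| 0.5 | 1.98 | 51% |

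**Check at the trial's size.** Use n = 1999 per group and an assumed effect of 0.10 SD in targeted patients. Power in all patients is Φ((1−f)·0.10/√(2/1999) − 1.96). Power in the subset is Φ(0.10/√(2/[1999(1−f)]) − 1.96).

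| f | All patients | Below guideline only |
|---|---|---|
| 0 | 88.5% | 88.5% |
| 0.05 | 85% | 87% |
| 0.10 | 81% | 85% |
| 0.2 | 72% | 81% |
| 0.5 | 35% | 61% |

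Under these assumptions the smaller, targeted analysis has more power at every f above 0. The gain is about 2 points at f=0.05 and 26 points at f=0.5.

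**A bound from the eligibility rule.** Each patient can meet at most one of the two guidelines, so the two values of f cannot sum to more than 1. Both may be small.

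**The case against.** The strongest reply is that the trial asks about one package. The aim is whether adding decision support for activity and diet affects outcomes in patients who miss at least one guideline. The all-randomised comparison answers that without bias. This stands. A reader might infer that the planned regression is biased or breaks intention to treat, or that it should be demoted to a supportive role. The protocol supports none of these readings. The estimate is diluted only relative to a narrower question, the effect on the behaviour that was alerted.

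Zero effect in untargeted patients is also an extreme. The tracking sheet can cover several behaviours at once, and practitioners are trained to address two or three together, so spillover is possible. Effort on one behaviour could also displace another, and an analysis limited to below-guideline patients would not show that for the behaviour already at guideline. Both are reasons to keep the all-randomised analysis.

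The size is unknown too. A reader might infer a heavy power loss for both outcomes, but f is not given. The Introduction says that tobacco users eat fewer fruits and vegetables and are less active, and the diet threshold is high, so f may be small, at least for diet. With a larger effect, 0.20 SD in targeted patients, power in all patients is still about 88% at f=0.5. The decision to keep offering the intervention rests on smoking cessation, not on these outcomes.

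One sentence under Intervention (Group A) joins the two guidelines with "and" when describing the alert. Read literally, patients missing only one guideline would get no alert, which would add to the dilution. Trial Design and the wording on specific risk factors favour the either-guideline reading used here.

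Finally, subgroup analyses often sit in the statistical analysis plan, which is not shown. But the protocol itself fixes the population and model for these outcomes. If the analysis plan already adds a below-guideline analysis, the point is met.

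**Conclusion.** The concern holds in a limited form. Entry by either guideline, patient-specific alerts and a single all-randomised regression together mean that each secondary estimate understates the effect of the alert on the behaviour it targets, unless spillover is as large as the direct effect. The randomised comparison remains valid for the package.

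With no effect in untargeted patients and equal variances, the estimate shrinks by the factor 1−f. Power of 80% becomes 78% at f=0.05 and 51% at f=0.5. Spillover would lessen the loss; larger variance among active patients would increase it for exercise minutes. That diet sits near the low end of f and exercise possibly higher is my assumption, not a protocol figure. The primary outcome and sample size are untouched. The change is still worth making, because it uses baseline data already collected and prevents a diluted null from being read as evidence that the alerts do not work.

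**What to change.** Keep the all-randomised intention-to-treat regression for both secondary outcomes. Pre-specify beside it, for each outcome:

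- The same regression on baseline and group among randomised patients below that guideline at baseline: under 150 minutes a week for exercise, and under 7 servings (women) or 8 servings (men) a day for fruit/vegetables.
- A group-by-baseline-guideline-status interaction in all randomised patients.
- A statement that conclusions about whether the system changes the targeted behaviour rest on the below-guideline analysis, and conclusions about the package rest on the all-randomised one.
- Use of the planned multiple imputation where the baseline item that defines the subset is missing, for example in a patient eligible on the other guideline alone.

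Baseline status comes from the enrolment survey and is not affected by allocation, so comparing arms within it preserves randomisation. Report the share meeting each guideline, so that readers can see the degree of dilution.

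The cost is wording in the protocol or analysis plan, with no new data. The downsides are a smaller analysis set and one more secondary estimate per outcome. If few patients meet a guideline, the interaction will be imprecise and should be read accordingly.

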### Data Security and Quality Assurance

Data will be stored in secure computerized files and the informed consent forms will be kept in locked cabinets in the study team’s locked offices. The STOP portal uses two different database encryption mechanisms (transparent database encryption and cell-level encryption) to protect the online data from intrusion. The study team will conduct monthly review of the data on the STOP portal to ensure the CDSS continues to operate correctly throughout the study.

### Ethical Approval and Trial Status

This study was reviewed by the Research Ethics Board at the Centre for Addiction and Mental Health, Toronto, Ontario, Canada (119-2018). This trial is registered with ClinicalTrials.gov (NCT04223336).

## Results

As of April 2020, interactive webinar training was delivered to STOP health care practitioners, and recruitment has started but is not yet complete. We estimate that recruitment will be completed in November 2020. Results will be reported in March 2021.

## Discussion

This clinical trial provides a novel method for addressing physical activity and fruit/vegetable consumption as part of a smoking cessation program. Smoking cessation programs continue to be essential public health initiatives. The literature shows that with every two individuals who quit smoking, at least one life is saved from a tobacco-related death [56]. Furthermore, in Ontario, physical inactivity and inadequate diet contribute to approximately 40% of all deaths [10]. If these risk factors can be addressed simultaneously, it could have significant positive effects on public health.

Moreover, delivery of this intervention via a web-based portal allows for rapid, system-wide implementation. The STOP program enrolls over 23,000 participants per year and the impact of this intervention could be widespread. The findings from this study can help inform future development and integration of interventions for other modifiable risk factors within smoking cessation programs.

We chose to conduct a hybrid type I design since our primary aim is to test the effects of a clinical intervention (adding a CDSS for physical activity and fruit/vegetable consumption) on relevant outcomes (smoking cessation at 6 months, and change in physical activity levels and fruit/vegetable consumption levels from baseline to 6 months). However, we also want to gather information on implementation outcomes from the study, including whether it changes the reach of the program, the adoption of the intervention (whether health care practitioners follow the recommendations of the CDSS and patients accept the resource), and potential barriers and facilitators to real-world implementation of the intervention. This design will provide high reward as the implementation research offers additional context that will help with understanding whether a clinical trial is effective or ineffective.

We chose to evaluate effectiveness via a randomized controlled trial with randomization at the individual level, as this is feasible (in both arms, the health care practitioner can respond directly based on the CDSS) and provides more power compared to cluster randomized controlled trials for detecting any clinically significant changes in the outcomes of interest [58].

There are a few potential study limitations that need to be acknowledged. Health care practitioners will not be blinded to the patient’s treatment allocation and will be seeing both intervention and control patients. The lack of blinding can lead to possible group contamination as health care practitioners may apply their knowledge from the intervention to the control group. The potential learning effect may decrease the effect of the trial. However, the self-monitoring resource for physical activity and diet are only accessible to intervention patients, which will help to reduce the cross-contamination. Randomization at the organizational level would not completely eliminate the risk of contamination as some health care practitioners work at multiple organizations.

The results of this trial will be disseminated through peer-reviewed publications and conference presentations. Results will also be presented and communicated appropriately to STOP health care practitioners and the funders for this initiative.

The findings of the study will provide much needed insight into whether other modifiable risk factors can be addressed simultaneously as a part of a smoking cessation program without affecting the individual’s ability and success in quitting smoking. If the results of the study are positive (ie, more intervention group individuals quit smoking) or show no negative effect on smoking cessation, we can continue to offer physical activity and diet interventions as part of smoking cessation programs. Our evaluation of the implementation of the study will also provide insights into whether CDSS interventions are an appropriate method for promoting physical activity and diet interventions as part of smoking cessation treatment.

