Given this association, smoking cessation programs appear to be well-suited for integration of health-promotion activities for other modifiable risk factors. There are established evidence-based methods for identifying and addressing modifiable risk factors as part of a clinical appointment [27-30]. Specifically, the Screening, Brief Intervention, Referral to Treatment (SBIRT) method has empirical support and requires little time from health care practitioners to deliver (approximately 5-10 minutes) [31]. Moreover, brief interventions have been found to be effective in addressing different types of modifiable risk factors, including physical activity [32] and diet [33]. With respect to the type of behavioral intervention offered, evidence shows that risk communication and encouraging self-monitoring are more effective than other behavior change techniques (eg, provision of educational materials and facilitation) in promoting successful behavior change [34]. However, the impact of implementing SBIRT for other modifiable risk factors within a smoking cessation program is unknown. Since tobacco use is the most important modifiable risk factor for health care practitioners to address, it is important to ensure that interventions for these other risk factors do not reduce the likelihood of quitting smoking successfully.

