### Objectives

The aims of this study are to: (1) assess whether adding a CDSS for physical activity and diet to a smoking cessation program affects smoking cessation outcomes, and (2) quantitatively and qualitatively assess the implementation of the study using the Reach, Effectiveness, Adoption, Implementation, and Maintenance (RE-AIM) framework.

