### Outcomes

The primary outcome of the study is self-reported smoking cessation at 6-month follow up. This dichotomous outcome will be measured by a negative response to the 7-day point prevalence abstinence question: “Have you smoked a cigarette, even a puff, in the last 7 days.” Researchers have shown that self-reporting for smoking status is highly consistent with biochemical assessments of smoking [51-54].

The secondary outcomes of the study will be a self-reported change in physical activity levels and fruit/vegetable consumption levels from baseline to 6-month follow up. Changes in physical activity will be assessed using an adapted Exercise Vital Signs screener [55] that consists of two questions: “On average, how many days per week do you engage in moderate-to-strenuous (vigorous) exercise (like a brisk walk)?” and “On these days, for how many minutes do you typically exercise at this level?” This screener has been validated against step counts [55]. Changes in fruit and vegetable consumption will be measured using a single question: “In a typical day, how many total servings of fruits and vegetables do you eat? (1 serving is 1/2 cup of fresh, frozen, or canned fruits or vegetables, or 1/2 cup of 100% juice. Please DO NOT include potatoes).”

These questions will be administered at the time of enrollment in the STOP program and at the 6-month follow up. Responses to the self-report questions for both the primary and secondary outcomes will be collected via phone or email. We will use the RE-AIM framework to organize our implementation evaluation, which is summarized in Textbox 1.

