### Sample Size

A sample size of 3998 (1999 per group) is needed to detect a clinically meaningful difference in smoking cessation outcome between groups at 6 months. Using past STOP data, and after accounting for nonresponse, we estimate the proportion of patients who will quit smoking at 6 months to be 0.26, and set α to .05 and the power to 80%. For the effect size, we use an absolute difference in proportions of 0.04, which is an established standard for clinical significance in smoking cessation [56].

Based on past experience in conducting trials using the STOP platform, we anticipate a loss to follow up of 20%. This increases the necessary total baseline sample to 4998 (2499 per group). Based on enrollment in 2017-2018, we estimate that the required sample size for the primary outcome will be achieved in approximately 7 months. However, as the recruitment and follow-up periods are likely to overlap slightly, we will monitor the follow-up rate being achieved. If this rate is lower than anticipated, we will consider extending recruitment to achieve an adequately powered analysis sample.

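### The plan lets a finding of no negative effect on quitting support continuing the intervention, but its only primary analysis is a test of difference and no criterion for concluding no harm is given

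*Protocol article*

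**What the plan says.** All references are to the protocol article.

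- **Background** makes the absence of harm part of the rationale: "it is important to ensure that interventions for these other risk factors do not reduce the likelihood of quitting smoking successfully".
- **Objectives** puts the first aim without direction: to "assess whether adding a CDSS for physical activity and diet to a smoking cessation program affects smoking cessation outcomes".
- **Outcomes**: "The primary outcome of the study is self-reported smoking cessation at 6-month follow up".
- **Sample Size** plans 1999 analysed per group to detect a difference. The text says "we estimate the proportion of patients who will quit smoking at 6 months to be 0.26" and, for the effect size, "we use an absolute difference in proportions of 0.04, which is an established standard for clinical significance in smoking cessation".
- **Statistical Analysis** gives one test for the primary comparison: "We will test for a group difference in our primary outcome using a chi-square test". The separate analysis plan is announced there for the imputation details only.
- **Discussion** links results to action. If more people quit in the intervention group, or if results "show no negative effect on smoking cessation, we can continue to offer physical activity and diet interventions as part of smoking cessation programs".

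No section gives a margin, an interval-based rule, or a definition of what would show no negative effect.

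**The concern.** The Background and Discussion ask whether physical activity and diet support can be added without costing quits. That is a no-harm question. The Sample Size and Statistical Analysis sections answer a different one, namely whether the arms differ detectably. A test of difference can reject equality, but failing to reject does not establish that a loss has been excluded.

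The decision at stake is whether to keep the alerts in a province-wide smoking cessation programme. If a non-significant chi-square were taken as showing no negative effect, the alerts could be kept on data that remain compatible with a loss larger than the plan itself treats as clinically significant.

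**Working it through.** **Inputs.** From Sample Size: quit proportion 0.26 (taken as the control rate), difference 0.04, alpha 0.05, power 80%, 1999 analysed per group, 20% loss to follow-up. From Randomization: 1:1 allocation. Assumption: the test is two-sided. The article does not say so, but the aim is non-directional and a one-sided test does not reproduce the stated size (1557 per group, or 1607 with continuity correction).

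**1. The plan's own figure.** For 0.26 versus 0.30, with mean proportion 0.28:

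n = [1.96·√(2·0.28·0.72) + 0.842·√(0.26·0.74 + 0.30·0.70)]² / 0.04² = 1977 per group, or 2027 with continuity correction. The stated 1999 lies between the two. Inflation: 1999/0.80 = 2499 per group and 3998/0.80 = 4998 in total, as stated. The sample size is sound for a test of difference.

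**2. Chance of a non-significant result when quitting truly falls.** With true loss d, intervention rate 0.26 - d and n = 1999, let SE₀ be the pooled and SE₁ the unpooled standard error. Then P(significant harm) = Φ[(d - 1.96·SE₀)/SE₁]. For d = 0.02, SE₀ = √(2·0.25·0.75/1999) = 0.01370 and SE₁ = 0.01369, so Φ[(0.02 - 0.02685)/0.01369] = Φ(-0.50) = 0.31. A significant result in favour of the intervention has negligible probability for losses of 2 points or more (0.0003 at 2 points).

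| True loss | P(significant harm) | P(non-significant) |
|---|---|---|
| 1 point | 0.11 | 0.89 |
| 2 points | 0.31 | 0.69 |
| 3 points | 0.60 | 0.40 |
| 4 points | 0.84 | 0.16 |

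**3. What a non-significant result can leave open.** With 26% quitting in control and an observed loss of 2.65 points, z = 1.94, which is non-significant. The lower 95% limit is -0.0265 - 1.96·√[(0.26·0.74 + 0.2335·0.7665)/1999] = -0.053, or about -5.3 points. A loss of 2.7 points is already just significant (z = 1.98), so 2.65 is close to the boundary.

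**4. What the planned sample could support under an explicit margin.** The article gives no margin, so a range is shown. With both true rates at 0.26, SE = √(2·0.26·0.74/1999) = 0.01387, and the 95% CI half-width is 2.7 points. The power for the lower limit to clear a margin of -m is Φ(m/SE - 1.96). The n for 80% power is 2·0.26·0.74·(1.96 + 0.842)²/m².

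| Margin | Power at 1999 per arm | n per arm for 80% |
|---|---|---|
| 4 points | 82% | 1888 |
| 3 points | 58% | 3356 |
| 2 points | 30% | 7551 |

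Multiple imputation may recover some information from those lost to follow-up. Even if all 2499 per arm counted in full, power would be 90%, 68% and 36% respectively.

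**The case against.** **The test is not blind to harm.** A reader might infer that this is a superiority test that can only find benefit. The article never uses that word. It asks whether the system affects cessation and tests for a difference. At a true 4-point loss the two-sided test has about 84% power, so the miss rate of 16% is below the 20% type II error the plan accepts. The 69% and 40% figures concern losses below the plan's own threshold of clinical significance. This stands, and it rules out calling the error rate uncontrolled at 4 points. It does not help with the interval: a non-significant result can still be compatible with a loss above 4 points.

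**The article does not say that p > 0.05 means no harm.** A reader might infer that the authors have committed themselves to that misreading. The Discussion says only that the programme can continue if results show no negative effect, and that wording could be taken to demand positive evidence. This also stands. The defect is that no other criterion is supplied.

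**The analysis plan may supply one.** It is not shown and could. But the article itself fixes the test, the size and the conclusion, and leaves only imputation details to that plan. This lowers certainty without removing the point.

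**Two amplifications should not be made.** A reader might say the plan expects contamination that would mask harm; the Discussion calls it possible and names a mitigating feature. A reader might also apply a 2-point loss to the 23,000 yearly enrolees (460 quits), but that count covers all enrolees, whereas trial eligibility also requires being below a guideline, online enrolment and contact details.

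**Conclusion.** The concern holds as a mismatch between the stated conclusion and the stated analysis. The chi-square test and the sample size are valid for the first aim. What they cannot do is show no negative effect by failing to reach significance. Non-significance would occur about 69%, 40% and 16% of the time at true losses of 2, 3 and 4 points, and a non-significant result can have a lower 95% limit near -5.3 points.

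These figures assume a two-sided 0.05 test, 26% quitting in control, 1999 analysed per arm and normal approximations.

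A reader might go further and conclude that non-inferiority at 0.04 should become the first primary test. The documents do not support that. The 0.04 is offered as a difference worth detecting, not as an acceptable loss, and recruitment had already begun. A 4-point margin also remains permissive: with a true 2-point loss the lower limit would still clear it about 31% of the time, since Φ[(0.04 - 0.02)/0.01369 - 1.96] = 0.31.

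**What to change.** Keep the chi-square test as the primary test. In addition:

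1. Report the risk difference (intervention minus control) with a two-sided 95% CI.
2. Replace the Discussion wording so that no negative effect is claimed only when the lower limit lies above a margin that is prespecified and justified before results are seen, and is no wider than -0.04.
3. If the lower limit does not clear the margin, call the no-harm question inconclusive and state the size of loss the interval excludes. A significant loss is reported as such.
4. State the power for the chosen margin, using the figures above or their equivalent.

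If no margin can be justified, drop the no-negative-effect inference and report only what the interval excludes.

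The cost is a change of wording in the protocol and analysis plan, plus the work of justifying a margin. No extra patients are needed for a 4-point margin. The downsides are that a non-significant result can no longer be called no negative effect by default, and that a margin tighter than 4 points would be underpowered at the planned size.
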